## Abstract

**Background:**

Charcot neuroarthropathy is a complication of peripheral neuropathy associated with diabetes which most frequently affects the lower limb. It can cause fractures and dislocations within the foot, which may progress to deformity and ulceration. Recommended treatment is immobilisation and offloading, with a below knee non-removable cast or boot. Duration of treatment varies from six months to more than 1 year. Small observational studies suggest that repeated assessment with magnetic resonance imaging improves decision-making about when to stop treatment, but this has not been tested in clinical trials. This study aims to explore the feasibility of using serial magnetic resonance imaging without contrast in the monitoring of Charcot neuroarthropathy to reduce duration of immobilisation of the foot. A nested qualitative study aims to explore participants’ lived experience of Charcot neuroarthropathy and of taking part in the feasibility study.

**Methods:**

We will undertake a two-arm, open study and randomise 60 people with a suspected or confirmed diagnosis of Charcot neuroarthropathy from five NHS, secondary care multidisciplinary Diabetic Foot Clinics across England. Participants will be randomised 1:1 to receive magnetic resonance imaging at baseline and remission up to 12 months, with repeated foot temperature measurements and X-rays (standard care plus), or standard care plus with additional three-monthly magnetic resonance imaging until remission up to 12 months (intervention). Time to confirmed remission of Charcot neuroarthropathy with off-loading treatment (days) and its variance will be used to inform sample size in a full-scale trial. We will look for opportunities to improve the protocols for monitoring techniques and the clinical, patient-centred and health economic measures used in a future study. For the nested qualitative study, we will invite a purposive sample of 10–14 people able to offer maximally varying experiences from the feasibility study to take part in semi-structured interviews to be analysed using thematic analysis.

**Discussion:**

The study will inform the decision whether to proceed to a full-scale trial. It will also allow deeper understanding of the lived experience of Charcot neuroarthropathy, and factors that contribute to engagement in management and contribute to the development of more effective patient-centred strategies.

**Trial registration:**

ISRCTN, ISRCTN74101606. Registered on 6 November 2017.

## Background

Charcot neuroarthropathy (CN) is a complication of peripheral neuropathy associated with diabetes which most frequently affects the lower limb. It can cause fractures and dislocations within the foot, which may progress to deformity and ulceration. The symptoms include redness, warmth and swelling in the foot and/or leg. This inflammation can lead to fractures in the bones and can damage joints, affecting the shape and function of the foot. It was first described 140 years ago [1]; however, it remains a poorly understood and frequently overlooked complication of diabetes [2].

Population-based studies have estimated a life time cumulative incidence for CN of 0.4 to 1.3% in people with diabetes, rising to 13% in people at high risk who attend diabetic foot speciality clinics [3]. In 2018, a regional survey of 205,033 people with diabetes in the East Midlands, UK, reported a point prevalence of 0.04% [4]. CN is associated with increased length of stay and use of medical resources [5].

The aim of treatment is to stop the inflammatory process, relieve pain and maintain foot architecture and so reduce the risk of future ulceration and amputation [6]. The current international consensus is that the foot should be immobilised in a below knee non-removable cast or boot, with weekly or fortnightly review by healthcare professionals working in specialist multidisciplinary diabetic foot clinics [7]. The immobilisation minimises the potential for any further damage to the foot structure. Immobilisation is continued until remission, defined as the absence of clinical signs of inflammation, measured using skin surface infra-red thermography and X-rays showing signs of bone healing and union [8].

The evidence base for the treatment of CN is weak. It is based on studies from a few centres which used retrospective designs and case note review methods using small sample sizes, typically in the range of 9–55 participants [3, 9–13]. Many studies failed to standardise monitoring, treatment and outcomes, which makes direct comparison between studies difficult.

Studies from the UK have shown a median time to remission of 9–12 months [9, 13, 14]. However, US studies report considerably shorter time to remission of 3–5 months [3, 10–12]. Studies from Brazil and Germany show remission times of 3–12 months and 3–6 months, respectively [15, 16]. Shorter treatment times could be related to reported differences in the relapse rates for CN, between 12 and 33% [13, 17–19], but without clear and consistent definitions for remission and relapse, this is unknown. There is also variation in the reported annual major amputation rates in people with CN from two different case series from hospitals in the USA—2.7% and 6.6% [20, 21].

The reasons for the variation are not understood but could include people’s characteristics at the start of the treatment, different techniques for monitoring CN, different protocols for the same monitoring techniques, variations in approach to off-loading and variability in study design. These could either underestimate or overestimate treatment duration.

Temperature difference between the feet is one of the most frequently used methods to monitor CN. It is recommended in the 2015 National Institute for Health and Care Excellence guidance on diabetic foot problems [22]. The most recent systematic review [8] published in 2013 recommends that immobilisation is continued until the temperature difference between the feet is less than 1–2 °C, and no further radiological changes on imaging have occurred. However, this recommendation is only based on level IV evidence, i.e. case series [8]. There is variability in the protocols used to measure the temperature difference between the feet. The most detailed protocol for measuring temperature discrepancy requires a 15-min acclimatisation period, controlled ambient air temperature and readings collected from nine different places on each foot [23]. In addition, plain X-rays demonstrate damage to the bone and joints rather than disease activity (inflammation).

Studies show inconsistency in the methods for monitoring and monitoring devices used [13, 17–19, 23–25]. These factors may overestimate or underestimate the degree of inflammation, so treatment may be discontinued too early or continued for longer than necessary. The presence of simultaneous bilateral foot disease or the absence of a contralateral limb through prior amputation invalidates the use of temperature measurement as a tool for identifying disease remission.

The National Institute for Health and Care Excellence recommends the use of MRI in determining a diagnosis of CN in the early stages of disease when no signs are evident on plain radiology [22]. However, serial MRI is not widely used in routine clinical practice as a tool to monitor for signs of disease remission in CN [26]. One prospective study using MRI with contrast reported that mean healing times were associated with contrast uptake assessed at baseline [27]. A further two retrospective studies looked at bone marrow oedema. One study reported decreasing bone marrow oedema in 69% of follow-up images [28], and the second study found a significant positive correlation between intensity of bone marrow oedema on MRI and clinical measures [29]. This emerging evidence suggests that MRI may be useful for the surveillance of active CN. The findings from MRIs could be adopted as the criterion standard for establishing disease activity and remission.

The use of MRI in monitoring CN therefore needs to be formally evaluated in a trial [30]. However, the evidence to support a full randomised controlled trial is presently insufficient. We will conduct a randomised feasibility study to understand the proportion of people who meet the eligibility criteria, the number of eligible participants recruited, the number of participants who receive an alternative diagnosis and the proportion of participants who withdraw. Time to MRI confirmed remission of CN with off-loading treatment (in days), and its variance will be used to inform sample size in a main trial. We will look for opportunities to improve the protocols for monitoring techniques in a future trial. We will examine the feasibility of a range of clinical, patient centred, and health economic measures. We are using a randomised controlled trial as it is considered the gold standard for evaluating efficacy in clinical research [31].

As part of the feasibility study, we will carry out a qualitative study to further the understanding of people’s experiences of living with CN and the factors that contribute to people’s engagement in their treatment. Previous qualitative studies have demonstrated the importance of people’s perspectives in order to promote engagement in the prevention and management of diabetic foot ulcerations [32–34]. What may be people’s views and experiences of CN is an under-researched area [35]. In the UK treatment times for CN are between 9–12 months [14], which is longer than those for foot ulceration, where treatment times are no more than 12 weeks for half of the people [36]. This means that evidence on people’s experiences of foot ulceration may not transfer to CN.

In summary, there is a lack of evidence to support the use of monitoring techniques in CN. Healthcare professionals rely on methods and devices which do not accurately reflect disease progression, and decision-making about discontinuing or prolonging immobilisation is challenging. A lack of understanding of people’s experiences of living with CN means their needs and wishes may be neglected with current treatments, and are not being considered when developing new treatment strategies and pathways.

## Aim and objectives

This study aims to explore the feasibility of using serial MRI without contrast in the monitoring of CN to reduce duration of immobilisation of the foot, in order to decide whether a large-scale trial is warranted. We will assess eligibility, recruitment, retention and withdrawal rates. Time to MRI confirmed remission of CN with off-loading treatment (days), and its variance will be used to inform sample size in a main trial. We will also examine the feasibility of collecting clinical, patient-centred and health economic measures. The nested qualitative study aims to explore the dimensions of lived experience of CN and the participants’ experiences of taking part in the feasibility study.

## Methods

### *Study design* (Fig. 1)

This is a two-arm, open, randomised controlled trial investigating the feasibility of using serial MRI to monitor CN. The study will last for a maximum of 3½ years. The study is divided into two phases: phase one, the active phase, will last until the CN is in remission or a maximum of 12 months, and phase two, the follow-up phase, will last for six months after remission (Fig. 1). The maximum time a participant will be in the trial is 18 months.

**Fig. 1 Fig1:**
[figure not shown]
Patient flow diagram

The decision to use an open label design was pragmatic: the MRIs will be reported by radiologists and interpreted by the healthcare professionals working in multidisciplinary specialist diabetic foot clinics. As the reporting of MRIs relies on comparison to previous images, this will indicate the trial arm the participant has been randomised to.

The trial has been reviewed and approved by East Midlands-Derby Research Ethics Committee, April 10, 2017, ref 17/EM/0288.

### Setting

The setting will be multidisciplinary specialist diabetic foot services at five NHS Hospital Trusts in England.

### Randomisation

A randomisation scheme has been generated by the trial statistician. Allocation will be stratified by centre. Participants will be randomised using a web-based randomisation process on a 1:1 basis to (a) immobilisation discontinued on the basis of clinical remission and determined by skin temperature measurement, which triggers an MRI (standard care plus) or (b) standard care plus and additionally the serial use of MRI at 3, 6, 9 and 12 months to identify disease remission and thus discontinuation of immobilisation (intervention).

### Sample size

As this is a feasibility study, a power calculation is not required. An allowance has been made for up to 10–15% of participants to be withdrawn from the study due to an alternative diagnosis. The sample size will be 60 people with 30 participants per arm, based on recommended sample sizes between 24 and 50 for a feasibility study [37, 38]. We will invite a purposive subsample of 10–14 participants from the feasibility study to take part in the qualitative study.

### Participants—inclusion and exclusion criteria

Participants will be people with diabetes as defined by the World Health Organisation [39] and a suspected or confirmed diagnosis of CN who are attending NHS multidisciplinary specialist diabetic foot services. They will be identified, recruited and consented by the healthcare professionals working in the foot clinics, and these will include podiatrists, nurses and doctors. The full inclusion and exclusion criteria are shown in Table 1. The main exclusion criteria were selected because (1) they are contra-indications to having an MRI scan, (2) bilateral disease prevents temperature comparison with the contra-lateral limb, and (3) co-morbidities may alter people’s inflammatory response. A confirmed diagnosis of CN can take several weeks, so participants will be recruited as early as possible to accurately collect length of time in below knee non-removable cast or boot. If the clinical team decides on an alternative diagnosis during the trial, then the participant will exit the study. We anticipate that alternative diagnosis will include infection, gout, arthritis, soft tissue injuries or deep vein thrombosis. Follow-up care will be provided by the appropriate clinical team.

**Table 1 Tab1:** Inclusion and exclusion criteria

Inclusion criteria	Exclusion criteria
Participants who are willing and have capacity to give informed consent.	People who have received a transplant and others receiving immunosuppressant therapy or using long-term oral glucocorticoids other than in the routine management of glucocorticoid deficiency. Participants on a low dose of oral glucocorticoids (< 10 mg for ≤ 7 days) are eligible to participate in the study.
People with diabetes as diagnosed by the WHO criteria http://www.who.int/diabetes/publications/diagnosis_diabetes2011/en/	Participation in another intervention study on active CN.
Age 18 years or over.	Contra-indication for MRI.
New or suspected diagnosis of acute CN (no previous incidence of acute CN within the last 6 months on the same foot) treated with off-loading.	Treatment for previous suspected CN on the same foot in the last 6 months.
Understand written and verbal instructions in English.	Suspected or confirmed bilateral active CN at presentation.
	Active osteomyelitis at randomisation.
	Previous contralateral major amputation.
	Inability to have an MRI scan.
	People receiving palliative care.

For the qualitative study, we have identified five participant characteristics which will purposively inform the sampling framework and will seek to maximise variation in sex, age, history of previous foot complications, duration of treatment for the current episode of CN and employment status. In addition to these factors, we will also ensure that participants equally represent both study arms.

### Outcomes

We will measure a range of feasibility, clinical efficacy and patient centred outcomes (Table 2). We will record time to MRI confirmed remission of CN with off-loading treatment (days), and its variance will be used to inform the sample size for a full-scale trial.

**Table 2 Tab2:** Feasibility, clinical efficacy and patient centred outcomes

Feasibility outcomes	Clinical efficacy outcomes (collected at all study visit)	Patient centred outcomes (collected at baseline, 3 monthly until remission, then at 1 and 6 months post remission)
The proportion of patients who meet the eligibility criteria	Number of new ulcerations on the index or contralateral foot	Health-related quality of life measured: Short Form 12 questionnaire (SF-12) [40] EuroQol-5D-5 L questionnaire (EQ-5D-5 L) [41]
The number of eligible patients recruited	Number of new infections on the index or contralateral foot	Hospital Anxiety and Depression Scale (HADS) [42]
The number of participants in which an alternative diagnosis is made during the active phase of the trial	Number of minor and major amputations on the index or contralateral foot at the end of the follow-up phase of the study	Pain as assessed by Visual Analogue Scale (VAS)
The proportion of patients that withdraw or are lost to follow-up. The term ‘withdrawal’ encompasses two potential scenarios: withdrawal due to loss of consent or withdrawal due to deaths	Number and severity of falls (Hopkins Fall Grading System) [43]	Patient diary
Statistical parameters of the key outcome measures, duration in off-loading to inform a sample size calculation for a definitive trial	The number of participants in each arm requiring further intervention for CN (e.g. further immobilisation) within 6 months of remission	
Ability to collect quality of life and resource use data		

For participants in the standard care plus arm, remission is defined as a temperature difference of ≤ 2 ^°^C which is maintained or improves on two separate consecutive occasions for a period of at least four weeks [8] or at the discretion of the clinical team when temperature difference is not valid; for example in the presence of bilateral foot disease. In the standard care plus arm, this will then trigger an MRI. In the intervention arm remission is defined as an absence of subchondral bone marrow oedema on MRI, as reported by a radiologist and the absence of clinical signs and symptoms of CN. The clinical team will interpret the results of the MRI report to determine remission.

The final visit will be six months after remission. During these six months, we will continue to monitor the foot using the standardised assessment of foot temperature for any clinical signs that the CN has relapsed. We have defined relapse as a temperature difference of > 2 °C compared to the contralateral foot maintained for two or more occasions or further changes on imaging. The final decision as to whether the CN has relapsed will be at the discretion of the clinical team.

We will explore the feasibility of collecting resource use and quality of life data, to inform the design of the health economics component of a future definitive trial. Data on all primary care and secondary care visits and admissions to hospital will be collected. Time off work and levels of informal care will also be assessed. We will use the qualitative interviews to gain a deeper, more detailed and rounded contextualised understanding of participants’ lived experience of CN and of taking part in this study.

### Planned interventions

*Standard care plus* participants will receive standard care for the assessment and management of CN and any other foot problems; alongside this, we will collect study measures (Fig. 2). If participants have not had a recent diagnostic X-ray or MRI (within the last 3 weeks, prior to randomisation), this will be requested. In this study, we have standardised the assessment of foot temperature to monitor CN by using the same device, the Thermofocus 01500A3®. Every 14 days, the temperature of both feet will be recorded at intervals of 5 min, starting at the removal of the off-loading device and up to 15 min. The sites where the temperature will be measured are based on the classification tool developed by Sanders and Frykberg [44]. We will classify the stage using the modified [45] Eichenholtz classification tool [46] and location of the CN [44] at baseline using anterior/posterior, oblique and lateral weight bearing X-rays.

**Fig. 2 Fig2:**
[figure not shown]
Schedule of enrolment, interventions and assessments. Active phase - while the CN is active participants will attend every 14 days, up to a maximum of 26 visits. Follow up phase – once CN is in remission participants will transfer into the follow-up phase of the study for six months. Classification of CN – accordingly to the Sanders and Frykberg and the modified Eichenholtz classification tools

*Intervention* in addition to standard care plus, participants in the intervention arm will receive serial MRIs at 3, 6, 9 and 12 months. Intervention participants will not undergo further MRIs once remission has been diagnosed, i.e. if remission is diagnosed at 6 months, the MRIs at 9 and 12 months will not occur.

### Study procedures (Fig. 2)

The schedule of enrolment, interventions and assessments is shown in Fig. 2. After giving written informed consent (see Additional file 2), participants will attend for visits every 14 days until remission. All visits will take place in multidisciplinary foot clinics. Wherever possible, study measurements and trial interventions will coincide with the participant’s existing clinic appointments. This will reduce study burden which is likely to help increase recruitment and retention rates. The study protocol (v1.3, dated 22 July 2019) is based on the Standard Protocol Items: Recommendations for Interventional Trials (SPIRIT) 2013 Statement for protocols of clinical trials (see Additional file 1).

Prior to participating in the interviews about the lived experience of CN, participants will receive a further patient information sheet explaining the purpose of the interview and will be asked to complete another consent form (see Additional file 3). All the qualitative interviews will be carried out by the first author (CG), using a semi-structured approach. The topic guide will include a number of probes designed to prompt the participant to increase the level of detail and depth of the information provided from the participants’ own viewpoint. Interviews will last approximately 30–40 min in a place of the participant’s choosing. The interviews will be audiotaped (with the participant’s permission) and transcribed in full to capture language and their own expressions.

### Analyses

#### Quantitative analysis

The feasibility measures including eligibility, recruitment, retention and withdrawals will be reported as point estimates with 95% confidence intervals. There is no intention to conduct any formal comparative analyses for these measures, though levels of missing data will be explored with respect to certain baseline characteristics, e.g. age and measures of disease severity. Variability in outcomes (e.g. standard deviation) will be estimated with 95% confidence intervals to inform the sample size calculations for a full-scale trial. Any between-group efficacy analyses will only be exploratory. There are no plans for any interim analyses.

We will assess progression of foot deformity by comparing X-rays at baseline, remission and six months post remission. We will measure the change in the calcaneal inclination, talar declination and talo-first metatarsal angle between the X-rays. People who have undergone previous minor amputation and/or previous orthopaedic surgical fixation of the foot which alters or removes the anatomical landmarks of the foot will be excluded from this analysis due to the absence of bony landmarks.

The main purpose of the economic analysis is to inform how the data on costs and effects would be collected within a definitive study. Thus, we will estimate completion rates and seek to identify big cost drivers, in order to inform this decision. A preliminary cost-effectiveness analysis will also be performed, although the findings will be treated with caution. As such, we will estimate the mean incremental cost and mean QALY gain associated with the intervention compared to standard care plus.

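### The main trial is to be sized from a plain variance of days to remission, but remission is observed only to 12 months, so a sizeable share of times is likely to be censored

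*Protocol article*

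**What the plan says.** The Abstract (Methods), the Background, the Aim and objectives and the Outcomes section all say that time to remission in days and its variance will feed the main-trial sample size. In the Outcomes section the wording is that "its variance will be used to inform the sample size for a full-scale trial". The Quantitative analysis section gives the statistic: "Variability in outcomes (e.g. standard deviation) will be estimated with 95% confidence intervals to inform the sample size calculations for a full-scale trial".

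The Study design section limits observation: the active phase "will last until the CN is in remission or a maximum of 12 months". The last scheduled scan matches that limit, since "participants in the intervention arm will receive serial MRIs at 3, 6, 9 and 12 months". On expected duration, the Background states: "Studies from the UK have shown a median time to remission of 9–12 months". The Setting section places all five sites in England.

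Table 2 words the sizing parameter differently, as "duration in off-loading to inform a sample size calculation for a definitive trial". The article does not say whether that duration is cut off at 12 months or how it relates to time to remission. It does not mention censoring or say how a participant still unremitted at 12 months enters the variance.

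**The concern.** A participant who has not remitted when the active phase ends has no observed time to remission, only a lower bound of 12 months. If the UK median applies, that is a substantial share of the sample. A plain SD needs a number for everyone. Leaving these participants out, or entering them at 365 days, removes the upper tail and shrinks the spread. It also pulls the two arm means together. Informing the main-trial sample size is one of the study's declared purposes and the stated use of this outcome, so the problem falls on the figure the study is meant to hand on.

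**Working it through.** The plan has no figure to reproduce: it gives no SD, target difference or main-trial size, and it states that no power calculation is needed for the 60 participants.

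**Inputs from the article.** Observation limit 12 months (Study design). UK median 9–12 months (Background). 60 randomised, 10–15% allowed for alternative diagnoses (Sample size), leaving 60 × 0.85 = 51 to 60 × 0.90 = 54.

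**Assumptions.** The article gives no distribution, so I take Weibull times with shape k from 1 to 3, a month of 30.44 days and a limit of 365 days. Main-trial sizes use two-sided 5% and 80% power, so (1.960 + 0.842)² = 7.849.

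**Step 1: share censored.** With median m in days, the share unremitted at 365 days is exp[−ln 2 × (365/m)^k].
- Median 12 months: 50% for any distribution, by definition of the median.
- Median 9 months (m = 273.9): 40% for k = 1, 29% for k = 2, 19% for k = 3.
- Median 7 months, as might hold if the intervention works: 31% for k = 1, 13% for k = 2, 3% for k = 3.

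At the UK median, that is about 10 (0.19 × 51) to 27 (0.50 × 54) evaluable participants without a remission time.

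**Step 2: the SD.** The scale is λ = m/(ln 2)^(1/k) and the full SD is λ√[Γ(1+2/k) − Γ(1+1/k)²]. For k = 2 this is λ√(1 − π/4) = 0.463λ, with λ = 329.0 at 9 months and 438.7 at 12 months. The other two columns come from integrating the same density up to 365 days.

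| Shape, median | Full SD | Remitters only | Non-remitters set to 365 |
|---|---|---|---|
| k = 2, 9 months | 152 | 88 | 101 |
| k = 2, 12 months | 203 | 88 | 93 |
| k = 3, 9 months (mildest tried) | 100 | 75 | 83 |
| k = 1, 12 months (most severe tried) | 527 | 104 | 126 |

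Both plain SDs are too small in every row. For k = 2 the remitters-only variance is low by a factor of (152.4/88.4)² = 3.0 to (203.2/88.1)² = 5.3.

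**Step 3: the difference in means.** With k = 2 and medians of 9 and 7 months:
- full means: 291.6 − 226.8 = 64.8 days;
- non-remitters set to 365: 257.6 − 216.9 = 40.7 days;
- remitters only: 213.2 − 194.6 = 18.6 days.

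**Step 4: effect on main-trial size.** Per arm, n = 7.849 × (SD₁² + SD₂²)/difference².

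(a) Plain SD with a target difference fixed from outside, here an assumed 60 days, so n = 2 × 7.849 × SD²/3600. SDs of 88, 93 and 101 give 34, 38 and 45. The full SDs of 152 and 203 give 101 and 180. The trial would be too small.

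(b) SD and difference both taken from the same data (k = 2, medians 9 and 7 months):
- full distribution: 7.849 × (152.4² + 118.6²)/64.80² ≈ 70;
- non-remitters set to 365: 7.849 × (101.5² + 99.4²)/40.68² ≈ 96;
- remitters only: 7.849 × (88.4² + 87.0²)/18.63² ≈ 348.

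Here the size goes up. The same ordering held at shapes 1, 1.5 and 3.

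**The case against.** The strongest reply is that the article does not commit to a naive calculation. The SD is given only as an example, the sentence covers all outcomes (for the questionnaires an SD is ordinary), and nowhere does it say that non-remitters will be dropped or set to 365 days. The article also condenses a fuller protocol, and an analysis plan not shown may handle censoring. This stands in part: the lack of Kaplan–Meier wording is not itself a fault, and the two naive rules above illustrate what could be done, not what the plan prescribes. What remains is what the article does fix, in several sections: the variance of days to remission as the sizing input, for an outcome it follows to 12 months only.

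Second, Table 2 points to duration in off-loading. If the main trial's endpoint were off-loading days within 12 months, the SD capped at 365 would be the right input and the full SD the wrong comparator. That is correct, but the article does not define the outcome so and elsewhere names time to remission.

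Third, censoring may be lighter. The Background notes that "US studies report considerably shorter time to remission of 3–5 months", and the intervention aims to shorten immobilisation. At a 5-month median with shape 2 only about 2% are censored and the capped SD is 0.97 of the full one. But the sites are English, and the article itself uses the UK figure when describing treatment times.

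A reader might infer from step 4(a) that the main trial will be three to five times too small. The documents do not support that. The comparison pairs a truncated SD with an untruncated difference, and the article does not say where the target difference will come from. Step 4(b) moves in the opposite direction.

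**Conclusion.** The concern holds as a fault in the stated sizing input. If the UK median applies, about 19–50% of times to remission would be censored, and a plain SD understates the SD of that outcome in every Weibull scenario examined. The direction follows from the 12-month limit. The amount rests on assumed shapes and on the UK median holding in both arms. The effect on the main trial has no fixed sign: too small if the truncated SD meets an external target difference, too large relative to full follow-up if SD and difference both come from truncated data.

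This is a should-fix, not a defect that undermines the study. It is a feasibility trial, its between-group efficacy analyses are exploratory, remission times are collected in any case, and nothing is lost that a better analysis of the same data could not recover.

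**What to change.** In the Abstract (Methods), Background, Aim and objectives, Outcomes and Quantitative analysis sections, replace the variance or SD of time to remission with censoring-aware parameters by arm, each with a 95% confidence interval: the Kaplan–Meier proportion in remission at 12 months, and the restricted mean time to remission up to 365 days with its standard error. State that the main trial will be sized on the endpoint matching the parameter used.

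Alternatively, define the sizing outcome as days in off-loading within 365 days of randomisation. Participants followed for the full 12 months then have a value whether or not they remit, and its SD is valid for that endpoint. Table 2 should carry the same definition, and the sections that name time to remission should be reconciled with it.

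Either route changes wording only and needs no new data for the time-to-event version. The cost is that a restricted mean or capped outcome describes the first 12 months only and says nothing about how much longer late remitters take.
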